### Main outcome

The main outcome is the change between baseline (M0) and 12-month follow-up (M12) of the PedsQL self-reported HRQoL score. The PedsQL generic HRQoL questionnaire has four multidimensional scales: physical functioning (8 items), emotional functioning (5 items), social functioning (5 items), and school functioning (5 items). The three summary scores are: total scale score (23 items), physical health summary score (8 items) and psychosocial health summary score (15 items). Each item uses a 5-point Likert scale from 0 (never) to 4 (almost always). Items are reversed scored and linearly transformed to a 0–100 scale, higher scores indicating a better HRQoL. Psychometric properties showed reliability, validity and responsiveness to clinical change over time [22]. After translation and cultural adaptation, the psychometric properties of the French version of the PedsQL appeared to be acceptable [23]. Two versions of the PedsQL questionnaire (13–17 and 18–25 years old) will be used for adolescents and young adults, respectively.

### Secondary outcomes (Table 2)

The following outcomes will be measured at baseline (M0) and 12-month follow-up (M12) and their changes over time will be analysed:Exercise capacity variables measured by a cardio-pulmonary exercise test (CPET): peak oxygen uptake (pVO2), ventilatory anaerobic threshold (VAT), and ventilatory efficiency (VE/VCO2 slope). As detailed in our previous trials involving exercise capacity assessment, CPET procedures in all participating laboratories will be harmonized [14, 15, 24].The level of physical activity with the Ricci and Gagnon questionnaire, composed by 8 items (total score < 16 points: no activity; 17–32 points: moderate activity; 33–40 points: intensive activity) [25].The level of knowledge with the Leuven knowledge questionnaire for CHD [26].The clinical outcomes: NYHA functional class, healthcare usage (primary and secondary care contacts, hospitalisation), and medication.The level of anxiety with the self-administered State and Trait Anxiety Inventory (STAI) questionnaire for young adults and the STAI-Children questionnaire for adolescents [27].The level of depression with the self-administered Beck Depression Inventory (BDI) questionnaire for young adults and the Child Depression Inventory (CDI) questionnaire for adolescents [28, 29].The parents-reported HRQoL score with the proxy version of the PedsQL for adolescents (aged 13–17 years old) [22].

**Table 2 Tab2:** Outcome measures

*Primary outcome*
Health-related quality of life score: PedsQL self-questionnaire (version 13–18 years for adolescents and version 18–25 years for young adults)
*Secondary outcomes*
Proxy version of the PedsQL for parents of adolescents (13–18 years old)
Level of anxiety (STAI self-questionnaire for young adults and the STAI-Children self-questionnaire for adolescents)
Level of depression (BDI self-questionnaire for young adults and CDI self-questionnaire for adolescents)
Level of physical activities (RICCI and GAGNON self-questionnaire)
Cardiopulmonary exercise tests parameters (peak VO2, VAT, VE/VCO2 slope)
Clinical outcomes: NYHA functional class, blood pressure, healthcare usage (primary and secondary care contacts, hospitalisation), and medication
The socio-economic status of the patient and/or the family (only at baseline)
Acceptability of the intervention to participants
Qualitative analysis (sample of patients from the intervention group)

### Sample size

The primary outcome is the change in the self-reported HRQoL score with the PedsQL instrument. In our previous HRQoL cross-sectional studies in patients with CHD [14, 30, 31] as well as in similar studies using patient related outcomes, a difference of less than 5 points seems irrelevant and a difference of more than 10 points is ideal, but rarely obtained in clinical trials [32, 33]. Therefore, we hypothesized to observe an increase in the overall HRQoL score of 7 ± 13.5 points (over 100). With a 80% power, a bilateral alpha risk of 5%, and potentially 20% of loss to follow-up and/or missing data on the primary outcome, we need to include 100 patients in each group.

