**Methods:**

Multicentre, randomised, controlled, parallel arm study in CHD patients aged from 13 to 25 years old. Patients will be randomised into 2 groups (education program vs. no intervention). The primary outcome is the change in self-reported HRQoL between baseline and 12-month follow-up. A total of 100 patients in each group is required to observe a significant increase of the overall HRQoL score of 7 ± 13.5 points (on 100) with a power of 80% and an alpha risk of 5%. The secondary outcomes are: clinical outcomes, cardiopulmonary exercise test parameters (peak VO2, VAT, VE/VCO2 slope), level of knowledge of the disease using the Leuven knowledge questionnaire for CHD, physical and psychological status.

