### Statistical analysis

All included subjects will be considered in the description of the population. An intention-to-treat analysis will be used, and each randomized subject will be analysed in his/her treatment arm. A per-protocol analysis, including all randomized subjects with a valid primary efficacy measurement and with no important protocol deviation (patients who have successfully completed the transition program) that could affect the evaluation of the main outcome, will also be carried out for parameters to assess the impact of the program when compliance is good (> 80% participation in sessions).

A description of the baseline characteristics of each group will be made by giving the frequencies of the different categories for the qualitative variables and the mean with standard deviation or median with interquartile range for continuous variables. In case of non-comparability of the groups, an adjustment or stratification (in case of interaction) on the potential confounding factors will be considered in a sensitivity analysis.

The change in the self-reported HRQoL total score, as well as the changes of the 2 summary and the 4 dimensions scores, will be compared between the two groups using student test or Man-Whitney test, according to the distributions. The effect size will be calculated using Cohen’s d and its 95% confidence limits.

The statistical significance will be set at 0.05 and analyses will be performed using Statistical Analysis Systems version 9 (SAS Institute, Cary, NC, USA).

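### The 80% power is attached to a 7-point increase with no comparator; for the planned between-arm test, 80 evaluable patients per arm give about 90% power at 7 points, or 80% at about 6

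*Protocol article*

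**What the plan says.** The Main outcome section defines the endpoint as a change within each patient: "The main outcome is the change between baseline (M0) and 12-month follow-up (M12) of the PedsQL self-reported HRQoL score". The Statistical analysis section says that the changes in the total score and its components "will be compared between the two groups using student test or Man-Whitney test, according to the distributions". The primary contrast is therefore the difference between arms in the change from baseline to month 12.

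The planning effect is worded differently. The Sample size section reads "we hypothesized to observe an increase in the overall HRQoL score of 7 ± 13.5 points", and the abstract says that 100 patients per group are "required to observe a significant increase of the overall HRQoL score of 7 ± 13.5 points". Neither place says what the increase is measured against. The other inputs are 80% power, a two-sided 5% level, 20% loss or missing primary data, and 100 patients per group. The Study design section gives 1:1 allocation and regular follow-up for controls. No expected change in controls appears anywhere in the article.

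The sentence before the hypothesis gives the scale for the choice of 7: "a difference of less than 5 points seems irrelevant and a difference of more than 10 points is ideal, but rarely obtained in clinical trials".

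**The concern.** A power figure means something only for a stated contrast. Here the effect reads as a rise over time, while the test is a comparison of two rises. A reader cannot tell whether 7 points is the expected gain in the educated arm or the expected advantage over controls. Those differ by whatever change the controls show over a year.

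The power is also a figure that readers of the results will rely on. If the trial is reported as having had 80% power for 7 points, a null result or a confidence interval will be judged against the wrong sensitivity. So the check is whether 80% belongs to the planned between-arm test at 7 points and, if not, what the design does deliver.

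**Working it through.** **Inputs from the protocol article.** Effect 7 points and SD 13.5; two-sided alpha 5%; power 80%; loss 20%; 100 enrolled per arm, 1:1. Evaluable per arm: 100 × (1 − 0.20) = 80.

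**Assumption.** 13.5 is the SD of the baseline-to-month-12 change. This is the natural reading, since the figure is attached to the increase itself, but the article does not say so outright.

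**Step 1. Reproduce the stated sample size, with 7 as the between-arm difference.**

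n per arm = 2 × (1.960 + 0.842)² × 13.5² / 7² = 58.4, rounded up to 59 (60 by the noncentral t).

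Allowing for 20% loss: 59 / 0.8 = 74, or 60 / 0.8 = 75. The stated 100 is not reproduced. Planning for the Mann-Whitney test does not close the gap: with its efficiency of 0.955 under normality the figure is 79 per arm, and with the worst-case 0.864 it is 88.

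Two other pairings do fit 100:
- 7 points at 90% power: 79 evaluable, 79 / 0.8 = 99 enrolled.
- 6 points at 80% power: 80 evaluable, 80 / 0.8 = 100 enrolled.

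**Step 2. Power that the design delivers.**

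Standard error of the between-arm difference = 13.5 × √(2/80) = 2.13.

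Power ≈ Φ(difference / 2.13 − 1.960).

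| True between-arm difference | Normal formula | Noncentral t |
|---|---|---|
| 7 | 90.7% | 90.3% |
| 6 | 80.3% | 79.8% |
| 5 | 64.9% | 64.4% |
| 4 | 46.6% | 46.1% |

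Difference with exactly 80% power: 2.13 × (1.960 + 0.842) = 5.98 points (6.02 by the noncentral t).

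**Step 3. If 7 points is only the intervention-arm rise.**

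Let c be the mean rise in controls, which is an assumption. The between-arm difference is 7 − c, so the table rows correspond to c = 0, 1, 2 and 3. Power stays at about 80% or more while c is at most 7 − 5.98 ≈ 1.0 point. It falls to about 64–65% at c = 2 and 46–47% at c = 3. If controls decline, power exceeds 90%.

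**The case against.** The strongest reply is that 7 was meant as a between-arm difference all along. The sentence before it sets the scale in terms of a difference, and 7 is chosen from that range. The requirement is given for each of two groups. A one-sample calculation on 7 ± 13.5 would need only about 30 patients, which is nowhere near 100. This stands as far as it goes: the between-arm reading is permitted, and under it the change in controls has no bearing on power. It does not rescue the stated figure, because on that reading the power at 7 points is about 90%, not 80%. In the other direction, the Discussion speaks of improvement in patients who undergo the programme, which fits the within-arm reading. The text does not settle the matter.

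Three stronger inferences are tempting and are not supported.

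- A reader might infer that the 80% holds only if controls do not change. The arithmetic contradicts this: there is room for a control rise of about 1 point, and a decline in controls raises power.
- A reader might infer from the abstract that a significant rise within the intervention arm would count as success. No within-arm test of the primary outcome is planned; the Statistical analysis section specifies a comparison between groups.
- A reader might infer that 13.5 is the SD of a score at one time, since the rationale begins "In our previous HRQoL cross-sectional studies in patients with CHD". Those studies are cited for the size of a relevant difference, not for the SD. A single-time SD with a baseline-to-month-12 correlation slightly above 0.3 would also lead to about 100 per arm (103 at exactly 0.3), but the article documents no such correlation. The origin of the SD may well be given in the full protocol.

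**Conclusion.** The point holds as a mismatch between the stated power and the planned test. The abstract and the Sample size section attach 80% to an increase without a comparator. For the comparison that will be made, with 80 evaluable per arm and an SD of change of 13.5, power is about 90% at 7 points, and 80% belongs to about 6 points.

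The documents do not show that the trial is underpowered. On the between-arm reading it has more power than it claims. On the within-arm reading it drops below 80% only if controls improve by more than about 1 point, and nothing in the article supports any particular control change. The results rest on the stated 20% loss and on 13.5 being the SD of the change. Neither the test nor the enrolment is in question. What needs correcting is a stated figure that readers will use to interpret the result.

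**What to change.** In both the abstract and the Sample size section, state the target as a difference between arms in mean change from M0 to M12 in PedsQL total score, with an SD of change of 13.5. Then give the power that matches it at 80 evaluable per arm, using one of two equivalent statements:

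- about 90% power for a 7-point difference; or
- 80% power for a difference of about 6 points.

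Once the effect is stated between arms, the calculation needs no assumed control change. Enrolment stays at 100 per arm, and the primary test is unchanged. The cost is rewording two sentences and restating one figure, with no extra patients or data.

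If the sponsor's own calculation used 13.5 as something other than the SD of the change, the matching power has to be recomputed on that basis before it is restated.

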## Methods

### Study design

The TRANSITION-CHD trial is an open label prospective, multicentre, randomised, controlled, parallel arm study. Patients will be followed for 12 months with an expected recruitment time period of 24 months.

Once the informed consent will be given, participants will be randomly allocated in a 1:1 ratio to either intervention (e.g. transition education program) or control group arms. In the control group, patients will have a regular non-modified follow-up with no formalized transition education program during the 12-month study period. However, they will be offered to participate in the transition therapeutic education program, once the 12-month study period is over (Fig. 1).

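### The printed inputs need 75 patients per arm, not 100; with 100 per arm and 20% loss the power for 7 points is about 90%, not the stated 80%

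*Protocol article*

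**What the plan says.** The sample-size section defines the primary outcome as the change in the self-reported PedsQL score and sets the planning effect: "we hypothesized to observe an increase in the overall HRQoL score of 7 ± 13.5 points (over 100" (the scale maximum). It then gives the design parameters, "With a 80% power, a bilateral alpha risk of 5%, and potentially 20% of loss to follow-up and/or missing data on the primary outcome", and the result, "we need to include 100 patients in each group". Allocation is equal: the study-design section says "participants will be randomly allocated in a 1:1 ratio". The statistical-analysis section compares the change between the two arms with a t test or a Mann-Whitney test, depending on the distribution.

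The abstract gives the same total: "A total of 100 patients in each group is required to observe a significant increase of the overall HRQoL score", with the same 7 ± 13.5, 80% power and 5% alpha. It does not mention the loss allowance.

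The document states no M0-M12 correlation, design effect or further inflation.

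**The concern.** Every input to a standard two-sample calculation is printed, so the reader can repeat it, and the printed result does not come out. The stated number is a third larger than the stated inputs require (100/75 = 1.33), or 50 patients more in total.

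This paragraph is the only justification given for randomising 200 adolescents and young adults. Either the power, the SD, the loss allowance or the number is not the one that was used. Until that is settled, the planned sensitivity of the trial is misreported. On the printed inputs it reaches 80% power at about 6 points rather than 7. That matters because the same section treats differences below 5 points as irrelevant.

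**Working it through.** **Inputs.** Difference δ = 7, SD σ = 13.5, two-sided α = 0.05, power 80%, loss or missing data 20% (all from the sample-size section); 1:1 allocation (study design); two-sample comparison of the change (statistical analysis). Standardised difference: 7/13.5 = 0.5185.

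**Attempt to reproduce 100 per arm.**
- Normal approximation: n = 2 × (z₀.₉₇₅ + z₀.₈₀)² × (σ/δ)² = 2 × (1.960 + 0.8416)² × (13.5/7)² = 2 × 7.849 × 3.719 = 58.4, so 59 evaluable per arm. With loss: 59/0.8 = 73.75, so 74.
- t test (noncentral t): 59.4, so 60 evaluable per arm. With loss: 60/0.8 = 75.

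The stated 100 is not reproduced.

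**Power at the stated number.** 100 × 0.8 = 80 evaluable per arm.
- Normal approximation: 7/(13.5 × √(2/80)) = 7/2.1345 = 3.279; 3.279 − 1.960 = 1.319; power 90.6%.
- t test: 90.3%.
- Difference detectable with 80% power at 80 per arm (t test): 6.02 points.
- SD at which 80 per arm gives 80% power for 7 points: 15.7.

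**Variants on the printed difference and SD** (per arm, including 20% loss, 80% power unless noted):

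| Variant | Per arm |
|---|---|
| One-sided 5% (normal approximation) | 58 |
| Inflation by × 1.2 instead of ÷ 0.8 (t test) | 72 |
| Mann-Whitney, efficiency 0.955 (normal data) | 79 |
| Mann-Whitney, efficiency 0.864 (worst case) | 87 |
| Two-sided alpha 0.025 (normal approximation) | 89 |
| Two-sided alpha 0.01 (normal approximation) | 109 |
| 90% power, normal approximation | 99 |
| 90% power, t test | 80/0.8 = 100 |

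**Routes to 100 at 80% power that need an unstated input.**
- If 13.5 were the SD of a single visit, the SD of change would be 13.5 × √(2(1 − ρ)), where ρ is the M0-M12 correlation (an assumption; none is given). This gives 104 per arm at ρ = 0.30, 97 at ρ = 0.35 and 75 at ρ = 0.50. An SD of change of 15.7, hence 100 per arm, corresponds to ρ of about 0.32.
- If 20% loss and a further 20% missing data were added together, 60/0.6 = 100. The text, however, gives one 20% for loss and missing data combined.

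**The case against.** The strongest reply is that the calculation may be sound and only its report incomplete. A larger SD of change, or a larger total loss, leads to 100 per arm at 80% power, and the full protocol may carry that assumption. This stands to the extent that the faulty figure cannot be identified from the article. It does not rescue the text: the section attaches 13.5 to the increase itself, gives a single combined 20%, and states no correlation.

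Several stronger readings are tempting, and the documents do not support them.
- A reader might infer that 90% was the intended power and that 80% is a misprint. The exact match at 90% is suggestive, but the other routes show that it is not proof.
- A reader might infer that the trial lacks the power it claims. On the printed inputs it exceeds it.
- A reader might infer that the recruitment target is unclear. Both the abstract and the sample-size section say 100 per group.
- A reader might treat the missing loss allowance in the abstract as a separate error. Taken literally, 100 evaluable per arm would give 95.4% power, but an abstract condenses, and the main text states the allowance.
- A reader might infer that 13.5 comes from cross-sectional data. The sentence citing such studies, alongside other studies and clinical trials, supports the 5-to-10-point relevance range and does not give the source of the SD.

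The wording of the effect as an increase is also a minor matter, since the analysis section makes clear that the change is compared between arms.

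**Conclusion.** The power and the sample size do not agree as written. On the printed inputs, 80% power needs 60 evaluable and 75 included patients per arm. The stated 100 per arm, with 20% loss, gives 90.3% power for 7 points, or 80% power for about 6.0 points.

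This rests on three assumptions: 7 is the between-arm difference in mean change, 13.5 is the SD of that change, and the test is the t test. With a Mann-Whitney test, power at 80 evaluable per arm would be about 89% (efficiency 0.955) or 86% (0.864), still above 80%.

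The error is conservative on these inputs and does not touch bias, type I error or the analysis. What a null result excludes will depend on the observed confidence limits, not on the planning power. The severity is moderate: a wrong planning figure that should be corrected, not a threat to validity.

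**What to change.** Keep 100 per arm. Check the sponsor's sample-size calculation, find which input produced 100, and print the matching statement in both the abstract and the sample-size section:
- if the printed difference, SD and loss were used: 90% power for 7 points (equivalently, 80% power for about 6.0 points);
- if 80% power for 7 points was intended: the SD of the M0-M12 change that gives 100 per arm, about 15.7. If the check instead turns up a different loss allowance, state that allowance.

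In either case, describe 7 as the between-arm difference in mean M0-M12 change and identify the SD as that of the change.

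The cost is one check of the sponsor's file and a wording change in two places. Enrolment, design and analysis stay as they are.

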### Statistical analysis

All included subjects will be considered in the description of the population. An intention-to-treat analysis will be used, and each randomized subject will be analysed in his/her treatment arm. A per-protocol analysis, including all randomized subjects with a valid primary efficacy measurement and with no important protocol deviation (patients who have successfully completed the transition program) that could affect the evaluation of the main outcome, will also be carried out for parameters to assess the impact of the program when compliance is good (> 80% participation in sessions).

A description of the baseline characteristics of each group will be made by giving the frequencies of the different categories for the qualitative variables and the mean with standard deviation or median with interquartile range for continuous variables. In case of non-comparability of the groups, an adjustment or stratification (in case of interaction) on the potential confounding factors will be considered in a sensitivity analysis.

The change in the self-reported HRQoL total score, as well as the changes of the 2 summary and the 4 dimensions scores, will be compared between the two groups using student test or Man-Whitney test, according to the distributions. The effect size will be calculated using Cohen’s d and its 95% confidence limits.

The statistical significance will be set at 0.05 and analyses will be performed using Statistical Analysis Systems version 9 (SAS Institute, Cary, NC, USA).

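### The plan promises to analyse every randomised patient, but the named primary test can use only patients with both PedsQL scores unless M12 is imputed

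*Protocol article*

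**What the plan says.** Five statements in the protocol article bear on this point.

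- **Population** (Statistical analysis): "An intention-to-treat analysis will be used, and each randomized subject will be analysed in his/her treatment arm".
- **Endpoint** (Main outcome): "The main outcome is the change between baseline (M0) and 12-month follow-up (M12) of the PedsQL self-reported HRQoL score".
- **Test** (Statistical analysis): for the change in PedsQL, total and subscales alike, the plan is that it "will be compared between the two groups using student test or Man-Whitney test, according to the distributions".
- **Expected missing data** (Sample size): the 100 patients per group allow for "potentially 20% of loss to follow-up and/or missing data on the primary outcome".
- **Second population** (Statistical analysis): "A per-protocol analysis, including all randomized subjects with a valid primary efficacy measurement and with no important protocol deviation".

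The only sensitivity analysis described deals with groups that differ at baseline: "an adjustment or stratification (in case of interaction) on the potential confounding factors will be considered in a sensitivity analysis".

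**The concern.** The population statement and the test do not fit together. The first covers everyone randomised. The second, run as written, covers only those who have both an M0 and an M12 score. Missing outcomes are dealt with by recruiting more patients, which replaces lost information but does not bring the lost patients into the comparison.

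What is at stake is bias in a result that will carry the intention-to-treat label. The trial is open label and the outcome is self-reported. The intervention arm alone has an individual educational visit, a one-day group session and a transfer visit about six months later. Controls keep their usual follow-up and are offered the programme once the study period is over. The programme also has retention in care among its aims, according to the Background. Loss that differs between arms, in amount or in kind, is therefore possible.

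**Working it through.** **Inputs.** From the Sample size section: effect 7, SD 13.5, two-sided 5%, power 80%, up to 20% missing, 100 per group. From Study design: 1:1 allocation. The completer-dropout gaps used below are assumptions; the documents give none.

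**1. The plan's own figure.** n per arm = 2 × (z₁ + z₂)² × SD² / effect².

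- At 80% power: 2 × (1.960 + 0.842)² × 13.5² / 7² = 58.4, so 59. With 20% loss: 59 / 0.8 = 73.75, so 74.
- At 90% power: 2 × (1.960 + 1.282)² × 13.5² / 7² = 78.2, so 79. With 20% loss: 79 / 0.8 = 98.75, so 99.

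The stated 100 per group does not reproduce at 80% power but fits 90%. This errs on the large side and is separate from the present point.

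**2. Who enters the test.** With 20% missing, 0.8 × 100 = 80 per arm have a change score. That is 160 of 200, so 40 randomised patients are left out unless M12 is imputed.

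**3. Is power the problem?** Power = Φ(7 / (13.5 × √(2/n)) − 1.960).

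- n = 80: Φ(3.279 − 1.960) = 0.906 (0.903 with the exact t distribution).
- n = 100: Φ(3.667 − 1.960) = 0.956.

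Power is adequate either way.

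**4. Is bias removed?** Let a share p of an arm be missing, and let g be the mean change of completers minus the mean change that the missing patients would have had. The mean change in the whole arm is (1 − p) × completers + p × missing. The completers' mean therefore differs from it by p × g. For the comparison between arms:

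bias = p × g (intervention) − p × g (control).

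Sample size does not appear in this expression. The bias is zero if the two terms are equal, for example with the same loss and the same gap in both arms. If loss in controls is unrelated to outcome (g = 0 there) and p = 0.20 in the intervention arm:

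| Assumed gap g | Bias = 0.2 × g | If completers show an effect of 7, effect in all randomised |
|---|---|---|
| 5 points | 1.0 | 6.0 |
| 7 points | 1.4 | 5.6 |
| 10 points | 2.0 | 5.0 |

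A gap of 7 means that the missing patients gain nothing from the programme: 0.8 × 7 + 0.2 × 0 = 5.6. A gap of 10 means an effect of −3 in them: 0.8 × 7 + 0.2 × (−3) = 5.0. That is an extreme case. A negative gap, or a gap in the control arm only, reverses the sign.

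**5. Does the wording resolve it?** A valid primary measurement is required explicitly only for the per-protocol set. By contrast, the intention-to-treat set should include patients without one. The named test, run without imputation, applies the same restriction to both sets.

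**The case against.** The strongest reply is that the article nowhere says patients without M12 will be dropped. A t-test on change can be run on imputed data, and a condensed protocol article commonly leaves imputation to the SAP. The intention-to-treat sentence can also be read simply as analysis by allocated arm, set against an adherence-based per-protocol set. This stands in part. The absence of a missing-data section is not the finding, and the article does not show that the analysis will be complete-case. What remains is that the text pairs an all-randomised promise with a test that, followed as written, cannot keep it.

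Four stronger readings are tempting, and the documents do not support them.

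- **Only the intervention arm has visits to attend.** Controls have regular follow-up, and the M0 and M12 assessments are not limited to one arm. Only the programme sessions are one-sided.
- **Patients who leave the programme are lost to the analysis.** A non-attender who completes the M12 questionnaire stays in.
- **The effect will be overstated.** The direction is unknown. Some features favour retention: patients intending to move region are excluded, and controls can look forward to the programme. The Background describes loss around transfer to adult care, not within a 12-month trial.
- **40 patients will be lost.** The 20% is an upper planning allowance that also covers missing questionnaires.

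Imputation from baseline data also cannot remove loss that depends purely on the unseen M12 value. That is correct, and it is why the fix includes a sensitivity analysis.

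**Conclusion.** The point holds for the analysis as written in the article. The promise to analyse each randomised patient and the unadjusted test on change cannot both be met for patients without M12 unless M12 is imputed. On the plan's own allowance this concerns up to about 40 of 200 patients. The consequence is possible bias and a label that may not fit, not a loss of power.

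The size cannot be derived from the documents. The shifts of 1.0 to 2.0 points rest on assumed gaps of 5 to 10 points, on 20% missing in one arm, and on loss in the other arm being unrelated to outcome. They matter because the Sample size section treats differences below 5 points as irrelevant and targets 7, a margin of 2 points. If the unseen SAP already specifies imputation, the remaining task is to bring the two texts into line.

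**What to change.** - **Primary comparison.** Compare the M12 PedsQL total score between arms in all randomised patients, adjusted for baseline PedsQL and age stratum, in place of the unadjusted test on change.
- **Missing M12.** Use multiple imputation by arm from data already collected: baseline PedsQL, age stratum, centre, CHD complexity, and the age-appropriate anxiety, depression and parent-proxy scores where they exist. Use sessions attended in the intervention arm only. Anxiety and depression instruments differ by age group and the proxy score exists only for adolescents, so the imputation model has to respect the age strata.
- **Sensitivity.** Add one analysis that lets missing patients do differently from observed ones, either delta-adjusted or control-based.
- **Alternative.** If this is not adopted, describe the analysis as complete-case by randomised arm.

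The cost is revised analysis wording and a few extra runs; no new data are needed. The downside is that the imputation assumptions must be stated. Baseline-based imputation leaves purely outcome-dependent loss uncorrected, so the sensitivity analysis is not optional.
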